### Statistical methods and power calculation

Approximately 2300 subjects with ≥2 risk-factors are required in each group (4600 subjects in total) to detect a 25% relative risk reduction at 5 years on the primary composite cardio-metabolic end-point of new onset T2DM, IGT, IFG, hypertension, albuminuria, renal and CVD events with intensive LSM. The study is powered at the 90% level with a type-1 error of 0.05 (2 sided) assuming a 15% incidence of the primary end-point in the control group and including allowance for 25% drop-out of subjects. The proposed 25% relative risk reduction of the composite outcome is derived from the effects of intensive LSM programme reducing the relative risk of new onset T2DM in South Asian IGT patients [1,6].

There will be a pre-specified interim analysis of the composite primary and secondary endpoints at 2 years, as requested by one of the funding bodies (IDF BRIDGES). This analysis will be performed by an independent statistician and the trial investigators will remain blinded to the full data analyses and interim results. All data related to interim analysis will directly forwarded to funding body by the independent statistician and will be strictly confidential and not for public dissemination/publication.

Descriptive statistics will be used for the analysis of demographic and clinical features of the cohort. Two-sided t-tests and chi-square (χ^2^) tests will be used to analyze the comparison between the groups at baseline and during follow-up. Survival curves will be calculated to estimate the cumulative incidence of the composite primary end-point and secondary end-points. The difference between the groups in the primary end-point will be tested by means of the two-sided log-rank test. All analyses of end-points are based on the intention-to-treat principle. Analyses will be performed using STATA software version 10 (Stata Corp, College Station, TX, USA).

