### Definition of primary cardio-metabolic end-points

▪ **New onset T2DM **as indicated by either a fasting plasma glucose of ≥7.0 mmol/l and/or a 2-hr plasma glucose concentration of ≥11.1 mmol/l during an annual follow-up confirmed by repeat 75 g OGTT as per World Health Organization (WHO) criteria [14] or initiation anti-diabetic treatment by the subject's family physician following confirmatory tests.

▪ **New onset IGT **is defined as a plasma fasting glucose <7.0 mmol/l and 2-h glucose 7.8-11.0 mmol/l and IFG as fasting plasma glucose between 6.1 to.9 mmol/l or 5.6 to 6.9 mmol/l [14,15].

▪ **New onset hypertension **is defined as mean brachial blood pressure from 2 readings taken following 5 minutes rest ≥140/90 mmHg or initiation of anti-hypertensive treatment commenced by the subject's family physician as per JNC-7 criteria [13]. In those below 18 years hypertension is defined as blood pressure that is, on repeated measurement, at the 95^th ^percentile or greater adjusted for age, height, and sex [13].

▪ **New onset albuminuria is defined as **urine albumin/creatinine ratio ≥2.5 mg/mmol in males and ≥3.5 mg/mmol in females from early morning sample confirmed on one repeat test.

▪ **New onset renal impairment is **defined as estimated GFR <60 ml/min or doubling of serum creatinine from baseline.

▪ **CVD events **are defined as fatal and not fatal events of Myocardial infarction (MI): Congestive heart failure (CHF): death due to clinical, radiological or post-mortem evidence of CHF, Stroke, vascular revascularisitation and admission for unstable angina.

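### The renal impairment end-point states no repeat test, unlike T2DM and albuminuria in the same list, so one low eGFR reading meets it; the likely effect on the composite is small

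*Protocol article*

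**What the plan says.** In *Definition of primary cardio-metabolic end-points*, new onset renal impairment is "defined as estimated GFR <60 ml/min or doubling of serum creatinine from baseline". No second sample is mentioned.

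The same list treats its other entries as follows:
- Albuminuria: "from early morning sample confirmed on one repeat test".
- T2DM: confirmed by a repeat glucose tolerance test.
- Hypertension below 18 years: needs repeated measurement.
- Adult hypertension: the mean of two readings.
- IGT and IFG: no repeat stated.
- CVD events: adjudicated by the independent board (*Independent advisory and data monitoring group*), which is given no such role for renal events.

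*Statistical methods and power calculation* counts renal events in the composite that sets the sample size: "hypertension, albuminuria, renal and CVD events with intensive LSM". The abstract, *Primary objective/end-point* and *Study design* list the composite without them. *Secondary objective/endpoints* names change in creatinine and eGFR, and also the individual components of the primary composite.

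**The concern.** A fixed cut-off applied to a single noisy measurement produces some false events. Where the true condition is rare, they can be a large share of all events recorded. This cohort is young and excludes diagnosed renal disease at screening, so new renal impairment is probably uncommon.

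False events that arise equally in both arms do not respond to the intervention. They pull the comparison towards no effect. The planned analysis is time to first event with a log-rank test, so a false renal event also uses up that participant's event and hides a later genuine one. The component itself would be hard to read, because low readings due to variation and true impairment would be counted together.

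**Working it through.** **1. The plan's own figure.** Inputs, all from *Statistical methods and power calculation*: "assuming a 15% incidence of the primary end-point in the control group"; "to detect a 25% relative risk reduction at 5 years", so 15% against 11.25%; two-sided 0.05; "The study is powered at the 90% level"; "including allowance for 25% drop-out of subjects". With p̄ = 0.13125:

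n = [1.96·√(2p̄(1−p̄)) + 1.2816·√(p1(1−p1) + p2(1−p2))]² / (p1−p2)² = (0.936 + 0.611)² / 0.0375² = 1,702 per group.

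1,702 / 0.75 = 2,270, within 3% of the stated 2,300. The figure reproduces. At 2,300 × 0.75 = 1,725 evaluable per group, power is 90.4%.

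**2. How often a single reading would fall below 60.** The documents give none of the inputs, so these are assumptions: true eGFR normal with mean 95-105 and between-person SD 12-16, within-person SD 6-10, independent errors, baseline reading at least 60, five annual readings. Each setting was simulated with 1,000,000 participants.

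| Setting (mean / between SD / within SD) | Any reading <60 | With one repeat also <60 | Ratio |
|---|---|---|---|
| Favourable (105/12/6) | 0.1% | 0.02% | about 6 |
| Mid (100/14/8) | about 1.6% | 0.3% | about 5 |
| Unfavourable (95/16/10) | 6.9% | 1.8% | about 4 |

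The ratio is about 3 at 95/16/6 (2.9% to about 1.0%). It exceeds 6 in one corner (105/12/10, about 0.8% to 0.07%). With one follow-up reading only, the unconfirmed rate is 0.03%-2.1% (mid case 0.5%).

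A second model, with proportional error (CV 5%-12%) and only participants whose true eGFR is at least 60, agrees in order of size. At mean 100-110 it gives 0.2%-2.1% unconfirmed and 0.05%-0.4% confirmed. At mean 90-95 it gives 0.8%-6.5% and 0.2%-1.4%.

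**3. Who is flagged.** In the mid case the median true eGFR of flagged participants is about 70, 77% are below 75, and 0.1% are at 90 or above.

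**4. Effect on the composite.** Let f be the false-event rate, equal in both arms, with 1,725 per group.
- Noise on top of the 15%: control 1 − 0.85(1−f), intensive 1 − 0.8875(1−f). At f = 1% these are 15.85% and 12.14%, a 23.4% reduction.
- Noise inside the 15%: control 15%, intensive 0.75(0.15−f) + f. At f = 1% this is 11.5%, a 23.3% reduction.

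| f | Power, on top | Power, inside |
|---|---|---|
| 0 | 90.4% | 90.4% |
| 0.1% | 90.2% | 90.0% |
| 0.5% | 89.3% | 88.3% |
| 1% | 88.2% | 85.8% |
| 1.6% | 86.8% | 82.5% |
| 2% | 85.9% | 80.1% |

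**The case against.** The strongest reply is that the text is silent: it does not say that a single value counts, and an article may condense a fuller definition. This stands in part. The renal entry nevertheless reads as a complete definition, in a list that states confirmation for T2DM and albuminuria. A reader applying it literally would count one reading.

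A reader might infer that most renal events would be test noise. The documents do not support that as a finding. It requires the false-positive rate to exceed the true incidence, and neither is given. The simulation holds true eGFR constant, so it contains no new renal disease. The share of flagged participants with true eGFR at or above 60 (about 87.5%-99% across the settings) follows largely from that.

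A reader might also picture people with plainly normal kidneys being miscounted. Step 3 shows otherwise: the false events come mainly from people somewhat above the cut-off, and their number depends on the assumed lower tail.

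Other points that stand:
- No follow-up creatinine schedule is stated, so five annual readings is an assumption.
- IGT and IFG also lack a stated repeat and probably contribute more events.
- The doubling limb is far less prone to noise.
- If the composite in *Primary objective/end-point* governs, dilution of the primary analysis disappears.

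**Conclusion.** The inconsistency is on the page: the renal definition has no confirmation step, T2DM and albuminuria do, and one low eGFR satisfies the definition as written. The direction of the effect is clear; its size is not.

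Power is essentially unchanged at 0.1% noise and falls by about 1 to 2 points at 0.5% and 2 to 5 points at 1%. A reader might take the fall to about 80% as the expected loss. That figure needs 2% noise, above the mid case, and needs the noise to displace real events within the assumed 15%. Nothing in the sample-size section says the 15% includes renal false positives. The loss to the whole composite is probably small. The clearer cost is a renal component that is hard to interpret.

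The point is minor. It applies to the primary analysis only if renal events belong to the composite, which the article leaves in conflict.

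**What to change.** In *Definition of primary cardio-metabolic end-points*, require eGFR below 60 (with baseline at least 60) to be confirmed on one repeat sample, as for albuminuria. Date the event at the first sample and apply the rule identically in both arms. The doubling limb may follow the same rule for consistency, though the noise does not lie there. Under the assumptions with mean eGFR 100-110, this keeps power at about 89%-90%.

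Separately, reconcile the abstract, *Primary objective/end-point* and *Study design*, which omit renal events, with *Statistical methods and power calculation* and the definitions list, which include them.

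The cost is one sentence and a repeat creatinine in a small minority (under 2% in the mid case, up to about 7% at the unfavourable end), which could share the visit for a confirmatory glucose or albumin test. A few transient falls, or falls first seen at the last visit without a repeat, would not count.

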#### Independent advisory and data monitoring group

An independent external expert advisory and monitoring board has been formulated which includes two experts from the MV-Diabetes Research Centre and Hospital in Chennai India (IDPP trial site) and one Sri Lankan expert from the Department of Community medicine, University of Colombo. This board will regularly review the progress of the DIABRISK-SL study and will also independently adjudicate on CVD events.

## Discussion

This study will be the first large population based study to determine the effect of a primary prevention LSM strategy on cardio-metabolic risk in a young urban population. This work will enable the characterisation of the natural history of cardio-metabolic disease in a unique at-risk population hitherto not studied in such detail or number. Importantly research project such as DIABRISK-SL enhance awareness of diabetes and associated risks amongst the study subjects, their friends and families. Such public health promotion is invaluable in countries with limited financial resources. The proposed intervention programme if successful may be implemented as a low-cost primary prevention tool in Sri Lanka and other similar low and middle income countries.

Our study will also determine the prevalence of T2DM, pre-diabetes, and cardio-metabolic risk factors in young urban Sri Lankans. We have also aimed to develop a method for identifying a sample at increased risk of T2DM and CVD for a randomised controlled trial. We hope to show that a simple screening strategy based on self-reported physical inactivity, family history of T2DM in first degree relatives, as well as obesity and increased WC provides an efficient method for identifying a sample with a high frequency of cardio-metabolic risk. More recently the entity of metabolic syndrome as a disease syndrome has been questioned [30]. However it is irrefutable that individual risk factors for CVD and T2DM cluster and inter-relate [11,12]. Furthermore in its purest form, as we will report with the exclusion of those with known T2DM or CVD and with detailed description of the individual risk components, it is a pre-morbid condition that could be useful in developing country specific public health intervention strategies [30].

This study will have the largest urban cohort below the age of 40 years in South Asia evaluated for cardio-metabolic risk. Our results will raise awareness of growing burden of T2DM and obesity in developing countries that is of major public health and economic importance and which requires urgent remedial actions [1,31]. The results of DIABRISK-SL will help advise and assist in the formulation of a national policy and guidance document for combating T2DM and associated non-communicable diseases in Sri Lanka [32].

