**Methods/Design:**

This is an open randomised controlled parallel group clinical trial performed at a single centre in Colombo, Sri-Lanka. A cluster sampling strategy was used to select a large representative sample of subjects aged between 5-40 years at high risk of T2DM and CVD for the intervention study. We have screened 23,298 (males 47% females 53%) healthy subjects for four risk factors: obesity, elevated waist circumference, family history of diabetes and physical inactivity, using a questionnaire and anthropometry. Those with two or more risk-factors were recruited to the intervention trial. We aim to recruit 4600 subjects for the intervention trial. The primary composite cardio-metabolic end point is; new onset T2DM, impaired glucose tolerance, impaired fasting glycaemia, new onset hypertension and albuminuria, following 5 years of intervention. The effect of the intervention on pre-specified secondary endpoints will also be evaluated. The study will be conducted according to good clinical and ethical practice, data analysis and reporting guidelines.

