**Discussion:**

DIABRISK-SL is a large population based trial to evaluate the prevalence of diabetes, pre-diabetes and cardio-metabolic risk factors among young urban Sri-Lankans and the effect of a primary prevention strategy on cardio-metabolic disease end points. This work will enable country specific and regional cardio-metabolic risk scores to be derived. Further if the proposed intervention is successful the results of this study can be translated and implemented as a low-cost primary prevention tool in Sri-Lanka and other low/middle income developing countries.

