### Study population and recruitment

We screened a population representative of the general population of Colombo District, the most populous urban district in Sri-Lanka, aged between 5 to 40 years to identify the prevalence of four risk-factors namely first degree family history (FH) of T2DM, physical inactivity, raised BMI and raised WC. The sampling strategy was designed to provide a sample that was representative of the age and sex distribution of the general population aged between 5-40 years in the Colombo district [3]. A list of schools, workplaces, universities and community organisations was made that were representative of the organizations and population aged between 5 to 40 years obtained from the most recent national census results. This list comprised of 65 organisations and each of these organizations was individually approached and eligible participants were invited to take part in the screening study. The screening survey took place between 1^st ^January 2008 and 30^th ^June 2009. The age and sex distribution of the screened population was regularly compared with the distribution of the reference population to ensure that the screened population was representative of the distribution of the general population aged between 5 and 40 years in the Colombo district. More than 95% of subjects and institutions approached agreed to participate. Subjects with a known history of T2DM, CVD, hypertension or diabetes and pregnant women were excluded from the initial sample. Subjects on lipid lowering drugs or anti-diabetic or anti-hypertensive drugs were also excluded.

Subjects with any active communicable or non-communicable chronic disease (NCD) such as cancer, asthma or other forms of chronic lung disease, depression, and tuberculosis were also excluded. A screening questionnaire (see additional files 1) was used to determine first degree family history of T2DM and the physical activity of the individual participants. Further information regarding socio-demographic factors was also collected.

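### The stated aim of determining the prevalence of diabetes and pre-diabetes in young urban Sri Lankans is wider than the design, which can give only undiagnosed disease among people with two or more risk factors

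*Protocol article*

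**What the plan says.** The prevalence aim appears twice in the protocol article without qualification. The Discussion says "Our study will also determine the prevalence of T2DM, pre-diabetes, and cardio-metabolic risk factors in young urban Sri Lankans", and the abstract's Discussion paragraph says "DIABRISK-SL is a large population based trial to evaluate the prevalence of diabetes, pre-diabetes and cardio-metabolic risk factors among young urban Sri-Lankans".

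Other sections describe who was assessed, and for what:

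- **Before screening** (Study population and recruitment): "Subjects with a known history of T2DM, CVD, hypertension or diabetes and pregnant women were excluded from the initial sample" and "Subjects on lipid lowering drugs or anti-diabetic or anti-hypertensive drugs were also excluded". The exclusion criteria at screening repeat this.
- **At screening** (abstract, Methods/Design): "We have screened 23,298 (males 47% females 53%) healthy subjects for four risk factors". The tools named are a questionnaire and anthropometry. The exclusion criteria then remove anyone with no risk factor or only one.
- **After screening** (abstract, Methods/Design): "Those with two or more risk-factors were recruited to the intervention trial".
- **Glucose testing** (Procedures): fasting glucose and the oral glucose tolerance test are among the measurements made at baseline, before randomisation.

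The Discussion also expresses the hope that the screening strategy "provides an efficient method for identifying a sample with a high frequency of cardio-metabolic risk".

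**The concern.** Population prevalence of diabetes counts diagnosed and undiagnosed cases across the whole population. Here the diagnosed cases are left out by design, and glucose is measured only in a subgroup chosen because it is at higher risk. The two features push in opposite directions. Selection on risk factors would tend to raise the observed frequency above the population value, and removal of known cases lowers it. Neither amount can be estimated from the data to be collected, so no later analysis can repair it.

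At stake is a descriptive conclusion about a whole population. A reader could take a figure from a selected subgroup as a national or city-wide prevalence. The screening claim has a related limit: without glucose results in people below the threshold, the data cannot show how much the rule enriches for disease or how many cases it misses.

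**Working it through.** **The plan's own figure.** The only sample size stated is for the randomised comparison: about 2,300 per group for 15% against 11.25% (15% × 0.75), two-sided 0.05, 90% power, 25% drop-out. The two-proportion formula with pooled variance under the null is

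n = [1.960 × √(2 × 0.13125 × 0.86875) + 1.2816 × √(0.15 × 0.85 + 0.1125 × 0.8875)]² / 0.0375² = 1,702 per group.

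Dividing by 0.75 gives 2,270, so the stated figure reproduces. It is not in dispute, and no size or precision is given for the prevalence aim.

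**Who has a glucose result.** The inputs are 23,298 screened and a recruitment target of 4,600 (abstract, Methods/Design). Taking the target as an approximation to the number tested:

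- 4,600 / 23,298 = 19.7% tested
- 23,298 − 4,600 = 18,698 (80.3%) not tested

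**What the tested group says about all screened.** Let f be the share tested, pH the prevalence in them, pL the prevalence in the untested, and r = pL/pH. Then

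prevalence among all screened = f × pH + (1 − f) × pL.

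The share of all cases that fall in the tested group is f / [f + (1 − f) × r]. The documents give neither pH nor r. With f = 0.197 and an assumed pH of 20%:

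| r (assumed) | Prevalence among all screened |
|---|---|
| 0 | 3.9% |
| 0.25 | 8.0% |
| 0.5 | 12.0% |
| 1 | 20.0% |

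The same observed 20% therefore fits a five-fold range. With no assumption about the untested, the bounds are 3.9% (none affected) and 3.9% + 80.3% = 84.2% (all affected).

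The share of cases that the rule would find is 71%, 50%, 33% or 20% for r = 0.1, 0.25, 0.5 or 1. Since r is never measured, these possibilities cannot be told apart.

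**Known cases.** If k is the share with known disease and u the undiagnosed share in the rest, total prevalence is k + (1 − k) × u. With u assumed at 2%, the total is 3.0% for k = 1% and 6.9% for k = 5%. The article plans no count of k.

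**The case against.** The strongest reply is that diabetes prevalence is not a formal objective. The general, primary and secondary objectives do not list it, and the recruitment section gives the survey's purpose as the prevalence of four risk factors, which all 23,298 people were assessed for. The wide wording stands only in the two discussion passages, and no estimator or denominator is fixed for it. This is right, and it limits the weight of the point. It does not remove it, because the article twice says what the study will determine and its methods do not allow that.

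It is also fair that the restriction of glucose testing to people with two or more risk factors is read from several sections together, and that the flow chart is not shown. But no section describes a tested subsample with none or one risk factor. The Discussion does mention leaving out known diabetes or cardiovascular disease, but only in connection with the metabolic syndrome.

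Some stronger readings are tempting and not supported:

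- **That a wrong prevalence will be published, inflated by a known factor.** This needs the subgroup figure to be reported as the population figure, which no section plans.
- **That the screening claim must go.** It is worded as a hope, about identifying a sample with a high frequency of risk. That frequency can be described in screen-positives. Only enrichment and missed cases cannot.
- **That recruitment through 65 organisations makes the confidence intervals too narrow.** The article plans no interval for a prevalence, gives no intracluster correlation, and may leave variance methods to a fuller document.
- **That 4,600 caps the number tested.** It is a recruitment target, and testing precedes randomisation, so more may be tested.
- **That the prospect of "country specific and regional cardio-metabolic risk scores to be derived" is an error.** No method or target population is fixed for the scores.

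**Conclusion.** The point holds for the glycaemic part of the prevalence aim. The design supports prevalence of the four screening risk factors among people without known disease, and of previously undiagnosed diabetes and pre-diabetes among people with two or more risk factors. It does not support prevalence of diabetes or pre-diabetes in young urban Sri Lankans.

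The illustrated range depends on two assumptions: that the recruitment target approximates the number tested, and that 20% of those tested have dysglycaemia. The conclusion that population prevalence cannot be estimated needs neither. It needs only that people with none or one risk factor go untested and that known cases are not counted.

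The claim should be reworded before results are reported. It concerns a descriptive statement only, and the primary end-point, the randomised comparison and its power stand.

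**What to change.** Restate the aim in the abstract and the Discussion as two narrower ones:

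- (a) prevalence of first-degree family history, physical inactivity, raised BMI and raised waist circumference among screened people without known disease;
- (b) prevalence of previously undiagnosed diabetes and pre-diabetes among people with two or more risk factors and no known disease.

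Narrow the screening sentence to the frequency of cardio-metabolic abnormality among screen-positives. State that nothing is claimed about enrichment over people with none or one risk factor, or about cases missed among them.

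The cost is a change of wording and a narrower descriptive claim. No new data are needed and the randomised comparison is untouched. Keeping the wider aim would instead require a count of known cases and glucose tests in a random subsample with none or one risk factor, weighted back to the screened population.
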